## Discussion

3

The present study constitutes a pioneering effort in the development of a platform aimed at optimizing psychosis treatment strategies by integrating a personalized approach centered on the individual characteristics of each patient. While existing literature supports the need to tailor interventions to the specific attributes of each individual, current clinical practice seldom implements this approach due, among other factors, to economic constraints and the limited scientific knowledge regarding the criteria that should guide treatment personalization.

MCT emerges as an ideal candidate for evaluating the feasibility of a personalized psychological treatment approach in psychosis for several reasons. Firstly, its efficacy has been extensively demonstrated both in the short and long term (12). Secondly, it is recommended in therapeutic guidelines as a first-line intervention for individuals with psychosis, addressing the psychological underpinnings of the disorder. Furthermore, MCT has shown positive outcomes across diverse psychosis subpopulations, suggesting its applicability to various diagnoses and disease stages. Moreover, its manualized format ensures interinstitutional comparability and facilitates implementation by mental health professionals with appropriate training. Additionally, its group-based application enhances cost-effectiveness compared to individual therapies.

The PERMEPSY project demonstrates a high degree of feasibility, supported by the consortium’s expertise in researching psychological interventions for psychosis, particularly MCT, as well as in the development of digital platforms and the application of machine learning. Prior to designing the randomized trial and the development of the predictive platform, the consortium conducted comprehensive systematic reviews of the literature to identify the most relevant variables associated with treatment response (11, 15, 19, 37, 38). These reviews, carried out by all partners according to their specific areas of expertise, ensured that the variables selected for inclusion in the retrospective harmonized database and the trial were both evidence-based and clinically meaningful. Variables identified by previous meta-analyses from researchers outside the consortium were also considered (12, 13, 48). This preliminary work strengthens the scientific foundation of the project and guarantees that the data collected are relevant for both the machine learning analysis and clinical decision-making. Moreover, the consortium has already collected and harmonized the necessary data for ML-based analyses and the creation of the platform prototype (39, 49, 50). The clinical team’s capacity to recruit patients in both past and ongoing studies further strengthens the feasibility of the trial.

Despite robust evidence confirming the efficacy of psychological interventions in symptom reduction and relapse prevention (51), only 10% to 25% of individuals with psychosis have access to such treatments (52). This is particularly concerning given that 50% to 75% of patients discontinue antipsychotic medication (5). The PERMEPSY initiative seeks to bridge this gap by providing a personalized psychological intervention tailored to patients’ specific needs. It is estimated that profiling patients and delivering individualized treatment could reduce relapse rates by over 70%, thereby helping patients regain a sense of purpose, enhancing their functional capacities, and increasing their overall recovery prospects. This approach is also expected to yield a significant reduction in both direct and indirect costs associated with psychosis.

Machine learning based technological solutions have the potential to enhance the identification of predictive variables for treatment response, thereby facilitating clinical decision-making. In the PERMEPSY study, a harmonized retrospective database was used to train a machine learning algorithm capable of predicting changes in key clinical and functional outcomes, such as positive symptoms, delusions, insight, self-esteem, between others. These predictions are generated based on composite patient profiles derived from pre-treatment data (39, 50). The platform thus supports clinicians to recognize objective problem areas, such as cognitive biases to address in the therapy. By combining the recognition of object problem areas from the ML algorithm with information about subjective concerns reported by patients, the MCT can be tailored to the individual needs. Beyond these clinical and cognitive predictors, this study also exploratorily examines whether blood biomarkers (inflammatory markers and SP transcription factors at selected sites) can contribute to refining predictive models of MCT response, offering preliminary insights into potential biological correlates of therapeutic change. Furthermore, incorporating a gender-sensitive approach in the early stages of treatment could further optimize outcomes. The development of the prototype platform and its implementation in clinical practice therefore represents a significant methodological advancement, enabling patient stratification based on data-driven insights and technology-assisted personalization (39).

While PERMEPSY constitutes an innovative initiative in applying personalized medicine principles to psychological interventions in psychosis, its implementation presents certain methodological challenges. The multicentric nature of the trial may introduce variability in MCT delivery, a factor that will be mitigated through a standardized training program, monthly supervision sessions, and staff mobility for trainers. Additionally, although the total sample size (*n* = 252) is sufficient to detect overall group differences, statistical power may be inadequate for conducting detailed subgroup analyses (e.g., by gender or comorbidities). To address this limitation, ML models prioritizing the most predictive variables will be employed, thereby reducing the risk of overfitting.

Finally, this study will also contribute to the development of knowledge regarding the ethical and legal aspects of patient stratification, as well as the regulatory frameworks for ML-based clinical decision support systems across various European Union countries and beyond. In fact, the consortium is already working on a regulatory roadmap in order to meet requirements for medical device certification, allowing the platform to be used in clinical settings. The findings may redefine mental health care standards by promoting more precise, cost-effective, and patient-centered interventions, in contrast to conventional therapeutic models. In line with this, the project provides an opportunity to adhere to current regulatory frameworks with the aim of facilitating the future translation of the developed platform into a certified medical device.

PERMEPSY represents a groundbreaking initiative in translating personalized medicine principles into the domain of psychological interventions for psychosis. By integrating advanced ML techniques within a transnational clinical trial, the project seeks not only to validate a predictive model but also to establish methodological foundations for future research in this emerging field. The potential benefits, ranging from resource optimization to reducing chronicity, justify the logistical and technical challenges inherent to its execution. The results of this trial could redefine mental health care standards, prioritizing precise, patient-centered interventions over outdated therapeutic paradigms.

## Ethics and dissemination

4

Patient data included in the PERMEPSY database will be collected and stored in compliance with the Ethical standards established by the World Medical Association in the Declaration of Helsinki at its current version (75^th^) (53, 54). The study was approved by the Sant Joan de Déu Ethics Committee (Reference: PIC-110-24), the Institute of Psychology, Polish Academy of Science (Reference: IP.403.21.2024), Ethics Committee of Valparaíso San Antonio Health Service of Chile (Reference: 48/2024), the local psychological ethics committee at the center for psychosocial medicine (LPEK) at the University Medical Center Hamburg-Eppendorf (Reference: LPEK-0796) and the Comité de protection des personnes Ile de France (Reference: 25.02907.000469).

Patient safety will be monitored throughout the study. Case report forms (CRFs) at each site have been designed to systematically record adverse events voluntarily reported by participants at each assessment point. Additionally, a modified version of the Patient-Reported Impact of Symptoms in Schizophrenia (PRISS) scale will be administered after each MCT session to monitor symptom changes during treatment and identify potential adverse effects. Any serious adverse events will be immediately reported to the designated responsible physician at each center, who will implement appropriate medical measures according to local clinical protocols and regulatory requirements. Serious adverse events will also be reported to local ethics committees in accordance with institutional and national regulations.

Personal data will be codified and stored securely and confidentially, not leaving each center’s archives. Upon completion of data collection from all centers, patient identification of patients recruited outside one’s own center will be unavailable through pseudonymization. The final prospective database will be anonymized and will not contain any personal data from participants. The anonymized prospective database will be openly available 10 years after the end of the project from the Cora repository (https://cora.csuc.cat/en/rdr-research-data-repository/). Access to the anonymized final dataset will be granted to consortium partners. The dataset will be made publicly available 10 years after project completion. The length of stored data will be 10 years after the end of the project, and destruction of stored data in open access is 10 more years after the end of the embargo period (20 years after the end of the project).

All participants included in the study will be asked to give informed consent for their data to be used in future related projects, for their data to be anonymized and shared in open access after 10 years, and for their pseudonymized data to be shared with consortium partners during the project. An additional informed consent form will be collected to gather blood samples and store them in the PSSJD biobank. Patients will also be informed that their data will be destroyed at the 20-year mark. The treatment, communication and transfer of data of all participants will comply with Regulation EU 2016/679 of the European Parliament and of the Council of April 27, 2016, on the protection of natural persons with regard to the processing of personal data and the free movement of such data and with the Organic Law 3/2018, of December 5th, 2018, on the Protection of Personal Data and guarantee of digital rights. The justifying legal basis of data processing is the patient’s signed consent, in accordance with the provisions of article 9 of EU Regulation 2016/679.

The project’s outcomes will be communicated in expert scientific conferences, peer-reviewed publications in scientific journals (in open access where applicable) and in community events or as plain-language summaries to reach participants and other lived experienced individuals, healthcare professionals, the public, and other relevant stakeholders. Trial outcomes will be registered and updated in public trial registries. This study protocol and all future publications will adhere to the Consolidated Standards of Reporting Trials (CONSORT) guidelines for transparent reporting of randomized controlled trials. The Standard Protocol Items: Recommendations for Interventional Trials (SPIRIT) checklist (55) can be found in the **Supplementary Table S4**. The project’s past, present and future dissemination actions can be viewed from the project’s website: permepsy.org.

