### Data collection

2.4

Pre-treatment, post-treatment, and follow-up assessments will be conducted by blinded, trained psychologists at each site. These evaluations will take place over the course of one to two interviews. Assessors will be trained in standardized administration of instruments to ensure equal collection across centers.

Nursing staff will be responsible for performing cubital vein blood counts for separation of peripheral blood mononuclear cells. Blood will be stored at 4°C until processed. Additionally, the transfer of samples to the Parc Sanitari Sant Joan de Déu (PSSJD) biobank will be requested following a prior agreement for participation in the study. The analyses will be conducted at the PSSJD Molecular Psychiatry Laboratory (SP1 and SP4 analysis) and the Hospital Sant Joan de Déu Clinical Laboratory (C-reactive protein and complete blood count). Blood will be collected from participants in the sites at UV and FSJD.

This study is in accordance with the World Medical Association’s Declaration of Helsinki and was approved by the Sant Joan de Déu Ethics Committee (Reference: PIC-110-24), the Institute of Psychology, Polish Academy of Science (Reference: IP.403.21.2024), Ethics Committee of Valparaíso San Antonio Health Service of Chile (Reference: N°48/2024), the local psychological ethics committee at the center for psychosocial medicine (LPEK) at the University Medical Center Hamburg-Eppendorf (Reference: LPEK-0796) and the Comité de protection des personnes Ile de France (Reference: 25.02907.000469). Since the study involves human participants, evaluations will be conducted once informed consent has been obtained. The personnel conducting the assessments, blood extractions, blood counts, and molecular analyses will be blind to the study condition assigned to each participant. All variables will be measured at baseline, post-treatment, and six months after completion, except for the DIAMOND and TEC scales, which will only be administered at baseline; the PRISS scale, which will be administered at the end of each session to monitor symptoms during treatment; patient satisfaction with treatment, which will be collected post-treatment and at follow-up; and the biological samples, which will be collected only within two weeks before the start of the intervention and within two weeks after its completion.

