Group sessions will be delivered by trained clinical psychologists or psychiatrists (https://clinical-neuropsychology.de/metacognitive-training-e-training/) with prior experience in MCT. All facilitators will undergo standardized training in both P-MCT and classical MCT, and monthly meetings will include supervision to ensure protocol fidelity. Data from all participants’ baseline assessment will be input into the platform, and its results will be used to personalize the homework for participants in the P-MCT condition only. Results from the MCT condition will be stored and only used to confirm the platform’s prediction accuracy.

In terms of adherence monitoring and ensuring protocol fidelity, participants are asked to complete a questionnaire after every session attended to record their symptomatology over the previous seven days, the completion of homework and their attendance to the session (session number and module attended). Other than the offered MCT sessions, participants will continue to receive their routine care through their usual center, including medication and any other non-MCT psychological treatment. Clinicians and MCT trainers will monitor for adverse events and discontinue the allocated intervention in case of worsening symptoms. Participants are allowed to drop out of the study at any point, and they are informed that they have the right to withdraw from their therapy group at any time when they sign the informed consent forms. Reasons for withdrawal, adherence to sessions and homework and reasons for missing data will be recorded.

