### Sample size calculation

2.6

To achieve a two-tailed size effect (Cohen’s *d*) of 0.5 with 95% power, using the total PANSS scores and balanced observations in the two groups, the estimated size is 210 in total. Considering 20% of loss to follow-up, we aim to include a total of 252 patients in the study.

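### Non-serious adverse events are collected by spontaneous report and session monitoring stops with attendance, so counts are likely too low and could be distorted by arm

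*Protocol article*

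**What the plan says.** The Ethics and dissemination section states that "Patient safety will be monitored throughout the study" and gives the method: case report forms "systematically record adverse events voluntarily reported by participants at each assessment point". Data collection fixes the assessment points: "All variables will be measured at baseline, post-treatment, and six months after completion", with listed exceptions.

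Between those visits, two session-level tools are described, which may be one form:
- Data collection lists "the PRISS scale, which will be administered at the end of each session to monitor symptoms during treatment". Ethics and dissemination adds that the scale "will be administered after each MCT session to monitor symptom changes during treatment and identify potential adverse effects".
- Interventions says that "participants are asked to complete a questionnaire after every session attended to record their symptomatology over the previous seven days".

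Other channels are also stated. Under Interventions, clinicians and trainers watch for adverse events, the allocated intervention is discontinued if symptoms worsen, and reasons for withdrawal and for missing data are recorded. Under Ethics and dissemination, serious events go at once to the responsible physician at the center and are also reported to the local ethics committee.

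**The concern.** The wording on volunteered reports is a stated method, not a detail left out of a condensed article. Followed as written, it records a non-serious event only if the participant thinks to mention it at a visit. The session tools are the only scheduled supplement. They stop when the participant stops coming, and for everyone they stop at session 10.

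A participant whose allocated intervention is discontinued for worsening leaves the session monitoring at that moment. If that person also misses the next assessment, the described rule yields no adverse-event entry for a non-serious event.

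Ascertainment may also be related to the intervention. Treatment adherence and insight are both H1 outcomes and both P-MCT homework domains. Adherence affects how many session forms exist. Insight may affect whether a participant recognises and mentions a worsening. Identical group sessions do not exclude either path, because the arms differ by homework aimed at these domains.

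At stake is whether the trial's harms data can be read at face value, overall and by arm. This matters more because the Discussion says the consortium is working towards medical device certification for the platform.

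**Working it through.** The protocol gives no adverse-event rate, no attendance by arm and no safety power figure, so there is no stated figure to reproduce. What can be checked is how the collection rule behaves.

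**Inputs from the protocol.** 10 sessions, once or twice a week; follow-up six months after completion; 252 participants, so about 126 per arm; "Considering 20% of loss to follow-up, we aim to include a total of 252 patients in the study".

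**Assumed inputs.** Equal true event risk q per session interval in both arms, 2% or 5%; attendance a between 60% and 90%; an event is picked up by a session form only if that session is attended.

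**1. Total count.** Expected recorded events per participant = 10 × q × a, so the share recorded equals a. At 80% attendance in both arms, one fifth of these events go unrecorded although the arms look equal. Participants with at least one event:
- q = 2%: true 1 − 0.98^10 = 18.3%; recorded 1 − (1 − 0.02 × 0.8)^10 = 14.9%.
- q = 5%: true 1 − 0.95^10 = 40.1%; recorded 1 − (1 − 0.05 × 0.8)^10 = 33.5%.

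**2. Comparison of arms.** With q equal, the ratio of recorded events is the ratio of attendance.

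| Attendance | Ratio of recorded events | At least one recorded, q = 2% | At least one recorded, q = 5% |
|---|---|---|---|
| 80% v 80% | 1.00 | 14.9% v 14.9% | 33.5% v 33.5% |
| 80% v 70% | 1.14 | 14.9% v 13.2% | 33.5% v 30.0% |
| 80% v 60% | 1.33 | 14.9% v 11.4% | 33.5% v 26.3% |
| 90% v 60% | 1.50 | 16.6% v 11.4% | 36.9% v 26.3% |

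**3. Participants who leave.** Suppose 15% truly worsen in each arm, and 20% of them in one arm and 40% in the other leave unseen. Recorded rates are 0.15 × 0.8 = 12% and 0.15 × 0.6 = 9%, about 15 and 11 of 126, a ratio of 1.33. If other channels catch half of the unseen cases, the ratio is (1 − 0.2 × 0.5)/(1 − 0.4 × 0.5) = 0.90/0.80 = 1.13. If they catch 90%, it is 0.98/0.96 = 1.02.

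**4. Coverage in time.** Ten sessions last about 5 weeks (twice weekly) or 10 weeks (weekly). With about 26 weeks to follow-up, the session tools span 5/31 = 16% to 10/36 = 28% of time on study. The rest relies on what is volunteered at the six-month visit, apart from serious-event reporting.

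**5. Loss.** 0.20 × 252 is about 50 participants. The protocol does not say at which visit they are expected to be lost, so this is a rough upper figure for those with no volunteered report at a given later visit.

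**The case against.** A reader might infer that adverse events are recorded only when volunteered, that patients who worsen and leave are simply missed, and that the better-attending arm will look less safe. The documents do not support that reading.

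- Clinicians and trainers monitor for events, serious events are reported without waiting for a visit, and reasons for withdrawal are recorded. These channels apply to the participant who worsens and stops coming.
- Blinded assessors measure positive symptoms at post-treatment and six months, and nothing makes those visits conditional on session attendance. Worsening of positive symptoms is therefore also measured, not merely volunteered.
- No attendance by arm is given, and the arms differ only in homework. At equal attendance the ratio is 1.00.
- H1 to H4 and their analyses contain no between-arm safety comparison and no claim of equal safety.
- The session form looks back seven days. In twice-weekly groups the next attended form can cover a missed session, so the ratios above are overstated there. A six-month report can likewise cover the preceding interval.
- This is a condensed article. How trainer observations reach the case report form may be set out in the full protocol or in the forms, so silence on that is not a finding.

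All of this stands, and it limits the point to non-serious events and to conditional distortion. It does not remove the point. The article states how participant reports are obtained, and that method is passive. A withdrawal reason is not an adverse-event record, and serious-event reporting does not cover non-serious events.

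**Conclusion.** The point holds for non-serious events. Collection by spontaneous report, with session monitoring tied to attendance, is likely to give counts that are too low, especially in participants who stop attending. The statement that safety is monitored throughout is only partly met by these tools.

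Distortion by arm is a possibility, not a demonstrated bias. It needs a difference in attendance or in willingness to report, together with weak back-up channels. Under the assumed rates, the ratio of recorded events is about 1.1 to 1.5 for attendance differences of 10 to 30 points if nothing else catches the events. In the example of participants who leave, 1.33 shrinks to 1.02 if other channels catch 90% of unseen cases. The protocol does not let one say where in that range the trial lies. It is a worthwhile change in collection method, and it does not affect the validity of the H1 analysis.

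**What to change.** In Ethics and dissemination, replace the reliance on volunteered reports with a standard open question plus a few fixed items, for example hospital admission, relapse and self-harm since the last contact. The blinded assessor asks these of every participant at post-treatment and six months, including those who stopped sessions.

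State that events noted by trainers or clinicians, and withdrawals due to worsening, are entered on the same adverse-event form. Someone other than the blinded assessor should enter them, since trainers handle the homework that distinguishes the arms. Report events by arm together with the number of participants actually asked at each visit.

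Contacting absentees after each missed session, or extracting clinical records for those who miss an assessment, would close more of the gap. These steps need extra site work and possibly wider consent, so they are optional.

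Cost: a few minutes at visits that already take place, a case report form page, and a wording amendment that may have to go to the five ethics bodies listed. Recorded counts will rise, which should be said when they are reported. Interventions schedules the sessions for October 2024 to April 2025. For visits already completed, the remedy is to report the method as passive and give the number assessed by arm.
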